**Date:**

6 August 2018

| Date of amendment              | Protocol version number | Type of amendment                              | Summary of amendment                                                                                                                                                                                 |
|--------------------------------|-------------------------|------------------------------------------------|------------------------------------------------------------------------------------------------------------------------------------------------------------------------------------------------------|
| 22 nd Nov 2012      | 1.1                     | In response to REC provisional opinion - minor | Typo corrections and addition of CTA, REC and ISRCTN numbers                                                                                                                                         |
| 20 th Feb 2014      | 1.2                     | Substantial amendment                          | Amendment to the wording of an exclusion criterion, additional details added to the statistical analysis section, update to the TSC and DMEC members, and other minor and administrative amendments. |
| 9 th June 2015      | 1.3                     | Substantial amendment                          | Update to recruitment period and total study duration.                                                                                                                                               |
| 28 th February 2017 | 2.0                     | Substantial amendment                          | Update to recruitment period and study duration, amendment to the wording of SAE reporting, amendment to the primary endpoint, update to the data collection section and other minor amendments.     |
| 1 st August 2018    | 3.0                     | Substantial amendment                          | Change in Chief Investigator, sponsor trust name change, data protection regulations update, parental responsibility text added and update to recruitment period and total study duration.           |

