## Statistical Analysis Plan (SAP) Amendments

| SAP version number | SAP section number | Description of and reason for change                                                                                                                                                                                                                                                                                    | Timing of change with respect to interim analysis/ final analysis/ database lock | Blind Reviewer |  |
|--------------------|--------------------|-------------------------------------------------------------------------------------------------------------------------------------------------------------------------------------------------------------------------------------------------------------------------------------------------------------------------|----------------------------------------------------------------------------------|----------------|--|
|                    |                    |                                                                                                                                                                                                                                                                                                                         |                                                                                  | Name:          |  |
| 2.0                |                    | Review of SAP prior to final analysis, decision made to transfer to new BCTU template which is a more comprehensive document. Text from previous SAP copied over to appropriate sections in new template. New sections in template, uses template text and/or text taken directly from SAP v1.0 or the latest protocol. | Prior to final database lock                                                     | Signature:     |  |
|                    |                    |                                                                                                                                                                                                                                                                                                                         |                                                                                  | Date:          |  |

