|                    | 4.3                | Following discussion with TSC and funder, the primary outcome was changed from URTI-related relapse following the first URTI to first URTI-related relapse, so URTI-relapse could occur after any URTI during the 12 month follow-up period.                                                                            |                                                                                  |                |  |
|                    | 4.7                | Sample size was revised during study, with the inflation rate applied to the sample size increased from 10-20% to 30%.                                                                                                                                                                                                  |                                                                                  |                |  |
|                    | 9.1                | The primary analysis will include covariate adjustment of the minimisation variable. Since the SAP was written, there has been a change in practice with the standard now for analyses to be adjusted for the minimisation variables included in the randomisation process.                                             |                                                                                  |                |  |
|                    | 9.3                | Text in SAP v1.0 on handling missing data for the secondary endpoints based on continuous data deleted. These outcomes are being analysed using repeated measures methods which can accommodate missing data.                                                                                                           |                                                                                  |                |  |
|                    | 9.5                | Analysis methods for primary outcome changed to reflect the use of regression models to adjust for the minimisation variables in the analysis.                                                                                                                                                                          |                                                                                  |                |  |

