|  |      |                                                                                                                                                                                                                                                                                                                                                                                                                                                                         |  |  |  |
|--|------|-------------------------------------------------------------------------------------------------------------------------------------------------------------------------------------------------------------------------------------------------------------------------------------------------------------------------------------------------------------------------------------------------------------------------------------------------------------------------|--|--|--|
|  |      | Intervention effect to be expressed as a risk difference and relative risk, rather than an odds ratio.                                                                                                                                                                                                                                                                                                                                                                  |  |  |  |
|  | 9.6  | Analysis methods changed to reflect the use of regression models to adjust for the minimisation variables in the analysis.                                                                                                                                                                                                                                                                                                                                              |  |  |  |
|  | 9.10 | Planned per-protocol analysis removed as considered uninformative now the primary outcome changed to any URTI-related relapse during the 12 months rather than assessing for relapse following first URTI, meaning for those who do not experience an URTI-related relapse during the 12 months which URTI is used for the assessment of adherence. Adherence to study medication is being assessed and summarised in a descriptive manner as described in section 7.2. |  |  |  |

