## **4.9. Interim analyses and stopping guidance**

A separate Data Monitoring Committee (DMC) reporting template will be drafted and agreed by the DMC including an agreement on which outcomes will be reported at interim analyses. The statistical methods stated in this SAP will be followed for the outcomes included in the DMC report, where possible.

Interim analyses of efficacy and safety are planned annually. The Haybittle-Peto approach will be used whereby all interim analyses use a difference of 3 standard errors (approximately  $p=0.002$ ) as a stopping guideline. These interim analyses will be reviewed by the DMC on an annual basis or more frequently if required by the DMC or Trial Management Committee

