#### **5.6. Unblinding**

This is a double-blind trial with the participants and clinicians remaining blind to treatment allocation. To maintain blinding, participants randomised to the control group receive the same number of study tablets that they would have received in the active treatment group through supplemental placebo tablets. The Trial Statistician has been unblinded to the intervention code for all of the interim analyses, and presented unblinded analyses to the DMC.

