### **9.10. Sensitivity analyses**

Sensitivity analyses will be limited to the primary outcome and will consist of:

- URTI-related relapse (Worse) / no URTI-related relapse (Best) and no URTI-related relapse (Best) / URTI-related relapse (Worse) for active and placebo groups respectively.

As an additional analysis, the number of URTI and non-URTl related relapses along with the number of participants who had a relapse in the modified ITT cohort will be compared to the number of non-URTl related relapses in that of the excluded cohort. It would be anticipated that those who have been excluded experience fewer relapses on the basis that they did not experience an URTI. However, if the numbers are similar it might be the case that some URTIs went unreported in this excluded population.

|                                                                                                                                                                                                                                                                                                                                                                                                                                                                                                                                                                                                                                                                                                                                                                                                                                                                                                                                                                                                                                                                                                                                                                                                                                                                                                                                                                                                                                                                                                                    |

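### The primary outcome was changed mid-trial, and the SAP plans no effect estimate for the outcome it replaced, relapse after the first URTI

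*Combined protocol and SAP*

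**What the plan says.** The protocol's amendment table lists, under version 2.0 of 28 February 2017, an "amendment to the primary endpoint". The SAP amendment log gives the content: "Following discussion with TSC and funder", "the primary outcome was changed from URTI-related relapse following the first URTI to first URTI-related relapse". Protocol 4.23.1 and SAP 4.3 carry the current outcome.

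On interim looks, SAP 4.9 states: "Interim analyses of efficacy and safety are planned annually". SAP 5.6 adds: "The Trial Statistician has been unblinded to the intervention code for all of the interim analyses", and says that unblinded results went to the DMC.

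The log has a column for the timing of each change relative to the interim analyses, the final analysis and database lock. Its only entry is "Prior to final database lock".

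SAP 9.10 opens "Sensitivity analyses will be limited to the primary outcome and will consist of". What follows is best/worst-case imputation by arm, with an added descriptive comparison against the children excluded for having no URTI.

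**The concern.** When a primary outcome is replaced while a trial is running, and some people connected with the trial have seen results by arm, readers will want to know whether the conclusion depends on the replacement. The usual answer is to report the replaced outcome beside the new one. This SAP plans no such estimate.

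The gap matters more here because the effect size that justified the trial was stated per URTI. The outcome that corresponds to that effect size is now the one without a planned analysis.

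**Working it through.** **1. What the SAP would produce for relapse after the first URTI**
- 9.5 (primary): current outcome only.
- 9.6 (secondary): any relapse, relapse rates, therapy changes, dose, adverse effects, questionnaires. First-URTI relapse is absent.
- 9.9 (subgroups): current primary outcome only.
- 9.10 (sensitivity): missing data and the excluded cohort.
- 9.7 (catch-all): simple summaries by group, with no adjusted effect, confidence interval or test.

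The data exist: protocol 4.21 collects details of every URTI and relapse at each follow-up visit. The denominator is also unchanged, because every child in the modified ITT set has, by definition, a first URTI.

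**2. The plan's sample size, reproduced** (protocol 4.28, SAP 4.7: 50% v 32.5%, 80% power, two-sided 5%)

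n per arm = [1.96·√(2·p̄·q̄) + 0.8416·√(p₁q₁ + p₂q₂)]² / (p₁ − p₂)², with p̄ = 0.4125
= [1.96·√0.4847 + 0.8416·√0.4694]² / 0.175² = 3.768 / 0.030625 = 123.04, so 124 per arm and 248 in total (stated: 250).

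Drop-out: 250 / 0.70 = 357.1, so 358 (stated: 360). Both figures reproduce.

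**3. Which outcome those inputs describe**

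The 50% is given as the share of URTIs followed by relapse. Its source, the Sri Lankan cross-over trial, contributes 19 relapses in 40 placebo-treated URTIs and 7 in 40 prednisolone-treated ones, and in the first period 10 of 22 children v 4 of 18. These are risks after one URTI, which is the replaced outcome. Power for it is 80.6% at 125 evaluable per arm. If only the 24% without a URTI are lost (180 × 0.76 = 136.8 per arm), it is 84.0%.

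**4. How many interims could have preceded the change**
- Upper bound: protocol version 1.1 is dated 22 November 2012, 4.3 years before 28 February 2017.
- Lower bound: protocol 4.29 reports children who had completed the trial by 12 July 2016, so randomisation had begun by about 12 July 2015, 1.6 years before.

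An annual schedule then implies roughly one to four interims. This is inferred, since no interim dates or count are given.

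**5. How far apart the two outcomes are** (assumptions: URTI counts are Poisson, 24% of children have none, and risk is equal and independent at each URTI)

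λ = −ln 0.24 = 1.427. P(any URTI-related relapse given at least one URTI) = 1 − (e^(−λp) − 0.24) / 0.76.
- p = 0.50: 1 − (0.4899 − 0.24)/0.76 = 67.1%
- p = 0.325: 1 − (0.6289 − 0.24)/0.76 = 48.8%

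| | First URTI | Any URTI |
|---|---|---|
| Control v active | 50% v 32.5% | 67.1% v 48.8% |
| Risk difference | 17.5 points | 18.3 points |
| Relative risk | 0.65 | 0.73 |
| Power, 125 per arm | 80.6% | 83.8% |

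**6. Whether they can disagree**

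A simulation of 20,000 trials used 125 children per arm, 50% v 32.5% per URTI, and Poisson counts with mean 1, 2 or 3 (zeros set to one). The two outcomes gave different significance verdicts in 11.6%, 18.4% and 21.3% of trials respectively.

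**The case against.** A reader might infer that the outcome was switched after years of unblinded efficacy results, by people who knew them. The documents do not support that. The number and dates of interims before February 2017 are not given. The parties documented as seeing unblinded results are the Trial Statistician and the DMC, whereas the log credits the change to discussion with the TSC and funder, and nothing says that either saw comparative data. The log also has a blind-reviewer column; its entries are not visible in the public version, but the column suggests a blinded check on SAP changes. This part of the objection stands in full.

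Nor is it true that the effect of the change is hidden. Both logs disclose it, the replaced outcome can be derived from collected data, and SAP 1 and 9.7 leave room for descriptive or exploratory reporting. What remains is the absence of a pre-specified estimate with a confidence interval.

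It is also tempting to treat reclassification as evidence of bias. Under the model in step 5, about 17 per 100 control children (67.1 − 50) and 16 per 100 active children (48.8 − 32.5) move from non-event to event. The shift is nearly equal in the two arms and the risk difference hardly moves, so it shows different event rates and nothing more.

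The replaced outcome is not wholly clean either. A child may have relapsed, and be on a higher prednisolone dose, before the first URTI (protocol 4.8), and study drug is not started during daily prednisolone (protocol 4.7). That argues for a supportive role, not against reporting it.

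Finally, the log explains its decision: "Planned per-protocol analysis removed as considered uninformative now the primary outcome changed to any URTI-related relapse during the 12 months". Whether to bring that analysis back is a trade-off, since it selects on behaviour after randomisation. The present point does not require it.

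**Conclusion.** The point holds as a gap in pre-specification. The primary outcome changed mid-trial, in a design with annual efficacy interims and an unblinded Trial Statistician, and the SAP plans no effect estimate for the outcome that the sample size inputs describe.

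The documents do not show that the change was informed by results, or that it biases the trial. Under the stated assumptions the two outcomes have similar power and similar absolute differences, but they would still disagree on significance in roughly 12% to 21% of trials. That is reason enough to show both. These figures rest on independent URTIs with equal risk and an assumed one to three URTIs per child. The documents give no distribution of URTI counts, and the 24% is a mid-trial figure among completers.

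**What to change.** Add to SAP 9.10: *URTI-related relapse within 14 days of the first URTI (original primary outcome), same modified ITT set and same adjusted models as section 9.5, reported as supportive beside the primary result.* In line with SAP 5.3, the first URTI should count whether or not study drug was taken.

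In the same revision:
- complete the SAP log's timing entry by stating when the outcome change fell relative to the interim analyses;
- reconcile protocol 4.8, part 3, which still describes the primary end point as built around the first URTI, with protocol 4.23.1.

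The cost is some SAP wording and a rerun of an existing model, with no extra patients or data. The downside is one more supportive result to report. Because the Trial Statistician is already unblinded, the addition cannot fully restore blind pre-specification, and the report should say so.

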# **3.BACKGROUND**

## **3.1 Study rationale / introduction**

Minimal change nephrotic syndrome is the commonest glomerular disease of childhood [Trompeter et al, 1985]. The presenting episode is treated with high dose oral prednisolone to which >90% make a complete response, responders receiving the diagnostic label of steroid sensitive nephrotic syndrome (SSNS) [Trompeter et al, 1985]. The optimum duration of prednisolone therapy at presentation remains unclear and is currently being investigated in the PREDNOS study (HTA 08/53/31, Chief Investigator [name]).

Following successful initial treatment, 70-80% of children develop disease relapses necessitating further courses of high dose prednisolone, and around 50% develop frequently relapsing disease [International Study of Kidney Disease in Children, 1982]. Long term low dose maintenance prednisolone therapy is the most commonly prescribed therapy to reduce relapse frequency, though a number will require additional immunosuppressive agents including levamisole, cyclophosphamide, ciclosporin, tacrolimus and mycophenolate mofetil (MMF).

Nephrotic syndrome relapses are associated with a risk of significant complications, including sepsis, thrombosis, dyslipidaemia and malnutrition [Webb, 2008]. The treatment of relapses with high dose prednisolone is associated with major adverse effects, including hip avascular necrosis, hypertension, diabetes and behavioural problems. Further, children are kept off school during relapses, resulting in impaired education performance and parental absence from work.

It is well recognised that at least 50% of relapses are precipitated by viral URTI, possibly mediated through release of cytokines [MacDonald et al, 1986]. Furthermore, in children with frequently relapsing SSNS, the development of an URTI results in relapse in over 50% of instances. Given these strong links between viral URTI and relapse, and the morbidity and cost associated with relapse and its treatment, it is logical that attempts are made to ameliorate the URTI-driven process.

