The secondary endpoints include both continuous and categorical data items. The dichotomous data (e.g. incidence of escalation of background immunosuppressive therapy) will be analysed as per the primary outcome. Continuous data (e.g. prednisolone dose, quality of life scores) will be expressed as means and standard deviations, with differences in means and 95% confidence intervals. Longitudinal plots of the data over time will be constructed for visual presentation of the data. Data will be analysed using mixed effect repeated measures models with the interventions specified as independent variables. Baseline data will be included in the model as a covariate.

Analyses will be of all randomised subjects using intention to treat, except for those who do not have an URTI following randomisation. Over the course of the study up to the 12th July 2016, the number of patients who have completed the trial without experiencing at least one URTI is approximately 24% which is higher than the originally estimated <10% at the start of the trial. Exclusion of these subjects will result in no bias as these drop-outs are not related to the treatment and should by chance be equally distributed across the two treatment arms (this will be monitored throughout the trial). Sensitivity analyses will be performed on the 12 month data analyses due to the issues raised above. These analyses will be fully outlined in the Statistical Analysis Plan, and will include analyses with subjects censored at point of treatment escalation.

The only subgroup analyses planned are by the background treatment regimen that the subjects are on at randomisation (no long-term treatment; on long term maintenance prednisolone therapy; on other immunosuppressant therapy with long term maintenance prednisolone therapy; on other immunosuppressant therapy without prednisolone); an analysis comparing those subjects on prednisolone versus those not on prednisolone; and an analysis comparing those subjects on other immunosuppressant therapy versus those not on other immunosuppressant therapy. The study is not powered to detect differences in treatment effect across these subgroups, so these analyses will be considered as hypothesis generating.

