#### **4.7. Sample size**

A total of 360 subjects will be recruited into the trial (180 into each group).

In children with frequently relapsing SSNS, the development of an URTI results in relapse in around 50% of instances. To detect an absolute difference of 17.5% (i.e. 35% proportional reduction) in URTI-related relapse rate (i.e. from 50% to 32.5%), with 80% power and  $\alpha=0.05$ , requires 250 subjects in total. Allowing for 30% drop out (e.g. subject withdrawal or lost to follow up, or subject not having an URTI during the 12 month follow up period), will require recruitment of 360 subjects. We therefore propose to recruit 360 subjects, 180 to each group.

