## **5.3. Analysis populations**

All primary analyses (primary and secondary outcomes including safety outcomes) will be based on the intention-to-treat (ITT) principle. Participants will be analysed in the intervention group to which they were randomised, and all participants shall be included whether or not they

received the allocated intervention following an URTI. This is to avoid any potential bias in the analysis.

The ITT population will not include all of the randomised population. Analyses will be based on a modified ITT population which will include only those participants who had an URTI over the 12 month follow up period. Excluding those participants who did not have an URTI will result in no bias as taking the study medication is conditional on them experiencing an URTI, and this should by chance be balanced between the two groups.

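### SAP 9.10's check for unreported URTIs compares numbers of relapses between cohorts of about 274 and 86 children and sets no denominator

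*Combined protocol and SAP*

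**What the plan says.** SAP 5.3 limits the analyses to a "modified ITT population which will include only those participants who had an URTI over the 12 month follow up period". SAP 4.7 sets the target: "A total of 360 subjects will be recruited into the trial (180 into each group". Protocol 4.29 reports that, up to July 2016, "the number of patients who have completed the trial without experiencing at least one URTI is approximately 24" per cent, against under 10% expected at the start.

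SAP 9.10 then adds an analysis of the children left out. On the modified ITT side it takes the number of URTI-related and non-URTI-related relapses, "along with the number of participants who had a relapse in the modified ITT cohort". These "will be compared to the number of non-URTl related relapses in that of the excluded cohort". Two outcomes are interpreted. The reassuring one: "It would be anticipated that those who have been excluded experience fewer relapses on the basis that they did not experience an URTI". The warning one: "if the numbers are similar it might be the case that some URTIs went unreported in this excluded population".

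The section gives no percentage, follow-up time, confidence interval, threshold or split by arm. It does not ask how many excluded children relapsed. The only other item in SAP 9.10 is a best-case/worst-case imputation of the primary outcome.

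**The concern.** A child counts as having had no URTI only because none was recorded, and recognition rests with the parents (protocol 4.7). The no-URTI share came out well above expectation, so under-reporting is a fair question. SAP 9.10 is the only planned SAP analysis that addresses it.

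The check reads similar numbers as the warning sign, but the two cohorts differ about threefold in size. The smaller cohort will have fewer relapses whether or not its URTIs were reported. Children who withdraw before any URTI also fall into the excluded cohort, so follow-up time may differ too, and the comparison does not allow for that. If the text is followed literally, the report could describe the exclusion as checked for under-reporting on the strength of a result that mainly reflects cohort size.

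**Working it through.** **Inputs.** Target 360 children, 1:1 (SAP 4.6, 4.7). No-URTI share 24% of completers, interim (protocol 4.29). Design risks 50% and 32.5% (SAP 4.7). Overall relapse rates of 0.9 (active) and 1.8 (control) per child-year, taken from the protocol's account of the Indian trial (protocol 3.1) and used here as an assumed range. URTI-driven share of relapses: protocol 3.1 says that "at least 50% of relapses are precipitated by viral URTI".

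**The plan's own figure.** Two proportions, 50% v 32.5%, two-sided 5%, 80% power, no continuity correction: 124 per arm, 248 in total (stated 250). Then 250/0.70 = 357.1, so 358 (stated 360). Both reproduce within rounding.

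**Cohort sizes.** 0.24 × 360 = 86.4 and 0.76 × 360 = 273.6, so about 86 and 274. The documents do not print these two numbers.

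**Counts if every excluded child had unreported URTIs and relapsed at the same per-child rate, with equal follow-up.** The rate cancels, so the ratio of counts is the ratio of cohort sizes:

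| Excluded | Excluded n | Modified ITT n | Excluded count ÷ modified ITT count | Rate multiple needed for equal counts |
|---|---|---|---|---|
| 10% | 36 | 324 | 0.11 | 9.0 |
| 20% | 72 | 288 | 0.25 | 4.0 |
| 24% | 86 | 274 | 0.31 | 3.2 |
| 30% | 108 | 252 | 0.43 | 2.3 |

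At 24%, in relapses: 86 × 0.9 = 77 v 274 × 0.9 = 247; or 86 × 1.8 = 155 v 274 × 1.8 = 493. The rate ratio is 1.0 in both cases. In Poisson and gamma-Poisson simulation at 24%, the excluded count never reached 80% of the other, and reached 50% in at most 0.3% of runs. At 30% excluded it reached 50% in about 3% to 18% of runs, and 80% almost never.

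**Excluded children at the untreated rate.** SAP 7.2 collects study-drug details only where an URTI is recorded, so excluded children have no reported courses. Put them at 1.8 and the modified ITT cohort at the two-arm mean, (1.8 + 0.9)/2 = 1.35: 86 × 1.8 = 155 v 274 × 1.35 = 370, a count ratio of 0.42. That is still fewer.

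**Counting children instead.** At the mean design risk of (50 + 32.5)/2 = 41.25%, 274 × 0.4125 = 113 modified ITT children would have an URTI-related relapse, more than the whole excluded cohort of 86. Excluded children at the 50% placebo risk give 43. (At 30% excluded the figures are 104 v 54.)

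**What a denominator adds.** If excluded children truly had no URTI and half of relapses are URTI-driven, their rate ratio is about 0.5 and the count ratio is 0.5 × 86/274 = 0.16. With complete under-reporting the rate ratio is 1.0 and the count ratio 0.31. Both count ratios read as fewer; the rate ratios differ twofold.

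**Precision.** The 95% factor around a ratio of 1 is exp(1.96 × √(1/E₁ + 1/E₂)), where E₁ and E₂ are expected relapses. Both arms together (274 v 86): 1.29 at 0.9 per year and 1.20 at 1.8; with strong overdispersion (gamma shape 1, assumed), 1.42 and 1.35. Placebo arm only (274/2 = 137 v 86/2 = 43): at 1.8, exp(1.96 × √(1/246.6 + 1/77.4)) = 1.29; at 0.9, exp(1.96 × √(1/123.3 + 1/38.7)) = 1.43. With the same overdispersion, replacing each 1/E by (1/rate + 1)/n gives 1.53 and 1.65.

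**The case against.** The best defence is that *number* is shorthand. SAP 4.8 frames the null hypothesis as a number of children and SAP 9.5 then tests proportions; protocol 4.28 does much the same. SAP 9.7 says that data outside the pre-specified outcomes are summarised by group, with percentages for binary items and means or medians for continuous ones. An analyst who knows the cohort sizes would probably add denominators. This stands as a prediction, but the text does not secure it. SAP 9.10 requires no percentage and no count of excluded children who relapsed, and SAP 9.7 does not lead to a rate per child-year.

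Four stronger readings are tempting, and the documents do not support them.

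- A reader might infer that the check can never raise an alarm. That follows only if raw totals are compared without regard to cohort size. SAP 9.10 calls it an additional analysis and attaches no test or consequence.
- A reader might infer that the arms are pooled. SAP 9.10 is silent on arms, and the SAP 9.7 default is by group.
- A reader might infer that this is the only support for the claim in SAP 5.3 that the exclusion causes no bias. That claim rests on study drug being conditional on an URTI and on chance balance, and protocol 4.29 says the balance will be monitored. Balance between arms cannot show under-reporting that is equal in both, but that is a different question.
- A reader might infer that shorter follow-up certainly lowers the excluded count. It may, but the documents give no figure.

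One further objection affects the remedy. Relapses within 14 days of an URTI are counted as URTI-related, so the non-URTI-related rate of modified ITT children is understated if all their follow-up is the denominator. At an assumed 1 to 3.9 infections per child-year (3.9 is (226 + 161)/100 from the Indian trial), non-overlapping windows remove 14/365 = 4% to 3.9 × 14/365 = 15% of follow-up. That rate cannot serve as a comparator without adjustment.

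**Conclusion.** The point holds as a defect in a supporting check. As written, SAP 9.10 compares numbers from cohorts of about 274 and 86 and treats similarity as the warning. At an equal per-child relapse rate the excluded cohort would show about 31% as many relapses (11% to 43% across excluded shares of 10% to 30%), which the text takes as the anticipated result. Similar counts would need about a 3.2-fold higher rate.

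This assumes that an interim share of completers applies to the full target of 360, that follow-up is equal, and that *number* is read literally. Withdrawals would shift the cohort sizes a little; the direction is the same throughout the range. The point does not show that URTIs went unreported or that the exclusion biases the treatment comparison, and it leaves the primary estimate, interval and p-value unchanged.

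**What to change.** In SAP 9.10, replace the numbers with two quantities, shown by arm for both the modified ITT and the excluded cohort:

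- relapses of any kind per child-year of observed follow-up;
- the proportion of children with any relapse.

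Give the excluded-to-modified-ITT rate ratio with its 95% interval from the SAP 9.6 Poisson model, using cohort as the explanatory variable and keeping the follow-up-time offset. Take the placebo arm as the main comparison, because excluded children report no study-drug courses and treated modified ITT children are not a like-for-like reference. State in advance that a ratio near 1 against the total relapse rate of modified ITT placebo children signals possible unreported URTIs. If the non-URTI-related rate is also used as a comparator, take the 14-day post-URTI windows out of the modified ITT follow-up time.

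The cost is a change of wording and one table from data already collected. The limitation is size: with about 43 excluded children per arm, the interval around a placebo-arm ratio of 1 spans a factor of roughly 1.3 to 1.65 on the assumptions above. That can separate 1.0 from 0.5. It would not resolve partial under-reporting: if half the excluded children had unreported URTIs, the ratio would be about 0.5 × 1.0 + 0.5 × 0.5 = 0.75. The interval should be reported and read with that in mind.
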